### Participant timeline

Time schedule of enrolment, interventions (including any run-ins and washouts), assessments, and visits for participants is depicted in Table 4.

**Table 4 Tab4:** Time schedule of enrolment, interventions and assessments according to the SPIRIT statement

	Enrolment	Allocation	Post-allocation					Close-out
TIMEPOINT	-T_0_	0	T_0_	1w	4w	12w	24w	24 weeks
ENROLMENT:								
Eligibility screen	X	X						
Informed consent	X							
*Data protection, Information material*	X							
Allocation		X						
INTERVENTIONS:								
*L. reuteri* Prodentis®-lozenges (DSM 17938, ATCC PTA 5289)								
Control lozenges								
ASSESSMENTS (NCT04598633* and NCT04606186*):								
Gingival Index			X	X	X	X	X	X
Probing Pocket Depth			X	X	X	X	X	X
Modified Plaque Index			X	X	X	X	X	X
Local cytokine concentration^1^			X	X	X	X	X	X
Oral microbiota^1^			X	X	X	X	X	X
ASSESSMENTS (NCT04606186*):								
Serum cytokine levels ^2^			X		X	X		
Frequencies of innate and adaptive immune cells^2^			X		X	X		

*Clinical Trial Registration number (registered at ClinicalTrials.gov in two parts: NCT04598633 for adolescents and NCT04606186 for adults); ^1^ samples from three oral niches: tongue, cheek, gingival crevicular fluid; ^2^ peripheral blood samples

### Sample size

The primary endpoint is the change of the Gingival Index from baseline to week four. The selected studies [45, 46, 86–88] were designed as randomized controlled trials (RCTs) and compared *L. reuteri* lozenges with control in various populations (Table 5). Effect size was calculated as follows: the change of the GI at a follow up visit and baseline was calculated. Then, the difference of this change in treatment and the control group was calculated and divided by the pooled standard deviation. Effect size varies across the studies. Notably, Iniesta et al*.* [88] reported no effect of lozenges compared to control. The other studies reported a significant effect [45, 46, 86, 87]. The smallest effect size of 1.00 was reported by Schlagenhauf et al*.* 2016 [45]. We use this worst case for the sample size estimation.

**Table 5 Tab5:** Effect size of *L. reuteri* lozenges versus control lozenges on Gingival Index (GI)

Paper	Effect size	Number of study participants
Schlagenhauf et al*.* [45]	1,00	55
Schlagenhauf et al*.* [46]	1,33	72
Vivekananda et al*.* [86]	2,79	30
Tekce et al*.* [87]	1,52	40
Iniesta et al*.* [88]	0,00	40

It cannot be assumed that the change in GI is normally distributed. Hence a Wilcoxon rank-sum test (WRT) is used to decide for significance. As the WRT is non-parametric, a sample size estimation for this test is not possible. Blair et al*.* 1980 [89] compared WRT with the t-test. The comparison showed that the power of the WRT is comparable to the power of t-test for various distributions. In the worst case, the WRT showed a power that was 5 percentage points lower than the power of the t-test. Thus, we will perform a power calculation for the t-test with 85% power and get the power of WRT of at least 80%.

Sample size estimation is performed with the following parameters: Two sample t-test, alpha = 0.05, Power = 0.85, one-sided test (superiority), H0: no difference between treatment and control and H1: difference in means between treatment and control is at least one SD (effect size > 1). The sample size calculation yielded as a result 16 study participants per arm, i.e. 32 participants in total. A greater effect size will yield smaller sample sizes. Sample size was calculated with Software R [90] using the function’power.t.test’ by the CCS ([name]). The formula for this sample size estimation is n = (σ/δ)^2^ * (z_1−α_ + z_1−β_)^2^ where δ/σ is the effect size and z_1−α_ is the 1-α-quantile of the t-distribution. We estimate that two study participants will drop out till week four. This corresponds to a low drop-out rate of 5%, in line with the selected studies [45, 46, 86–88]. Therefore, 34 patients have to be recruited. The analysis of the primary endpoint is applied to the per-protocol population. Therefore, the number of cases will be 17 study participants for each study and each control group: 34 adolescents (17 study participants for the study group, 17 study participants for the control group) and 34 adults (17 study participants for the study group, 17 study participants for the control group).

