## Methods/design

### Objectives

The trial aims to analyse probiotics as a possible preventive treatment approach during orthodontic treatment with fixed appliances. The primary objective is to study the influence of adjuvant intake of test versus control lozenges during the first 3 months of the orthodontic treatment of adolescent and adult patients with fixed appliances on the gingival index.The secondary objective is the investigation of the influence of adjuvant intake of test versus control lozenges during the first 3 months of the orthodontic treatment of adult patients with fixed appliances on clinical parameters, local cytokine expression and the composition of the oral microbiota at different time points during the first 6 months of treatment. Moreover, the secondary objectives for the adult group also include the analysis of the influence of adjuvant intake of test versus control lozenges on systemic parameters and inflammation at different time points during the first 3 months of treatment.

The null hypothesis is that there are no significant differences between patients with adjuvant intake of probiotics (*L. reuteri* Prodentis®) during the first 3 months of the orthodontic treatment with fixed appliances and patients with adjuvant intake of control lozenges concerning the following criteria: gingival Index (GI), modified plaque index (MPI), periodontal probing depth (PPD), local cytokine expression and composition of the oral microbiota (in one representative of each of the three oral metaniches: P (representing P—GCF), T (representing S—T—HP) and C (representing C—U) [52]), serum cytokine levels and frequencies of innate and adaptive immune cells in peripheral blood of adult patients.

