### Statistical methods

Descriptive analysis is applied according to the scale of measurement of the variable: Nominal and ordinal variables are described by counts and percentages. Interval scaled variables are described by mean and standard deviation, or robust estimators like quantiles if necessary. The number of missing and valid values are counted for every variable. Inference statistics is based on a frequentist basis with hypothesis tests, p-values and confidence intervals. Applicable tests for this two-arm study are the t-test, WRT and Chi^2^-tests, according to the scale of measurement of the variable. The significance level is set to 5%; confidence intervals are two-sided with a length of 95%. Corrections for multiple testing may be applied, when a hypothesis is tested in multiple subgroups. The protocol presented in the paper is according to the SPIRIT guidelines [92, 93]. The size of the populations is reported by the Safety Evaluation Set (SES), Full analysis Set (FAS) and the Per Protocol Set (PPS). If these populations have remarkably different size, all endpoints and demographics are reported for each population. The software R will be used for data analysis. The following analysis sets will be defined for the statistical analysis of this study: (1) Safety Evaluation Set: The SES is the subset of all subjects who were exposed to any study intervention at least once; (2) Full Analysis Set: The FAS is the subset of subjects in the SES for whom the primary endpoint is available (here: all subjects who have GI data available at baseline and at four weeks); (3) Per Protocol Set: The PPS is the subset of subjects in the FAS without major protocol deviations. One major protocol deviation is the noncompliant intake of lozenge. Further major protocol deviations may be defined during the study.

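### Each age group is sized on a one-sided 5% test, but the side of the deciding test is not fixed in the analysis section and does not match the two-sided 95% intervals

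*Protocol article*

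**What the plan says.** Under Sample size, the primary endpoint is the change in Gingival Index from baseline to week four, and the WRT decides significance. The article takes the WRT to lose at most 5 percentage points of power against the t-test, and so plans: "Thus, we will perform a power calculation for the t-test with 85% power and get the power of WRT of at least 80"%. The inputs follow: a t-test with alpha 0.05 and power 0.85, "one-sided test (superiority), H0: no difference between treatment and control", with the alternative that the "difference in means between treatment and control is at least one SD (effect size > 1"). This gives 16 per arm, 32 in total, and 34 after drop-out, separately for adolescents and adults.

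Two other sections bear on the decision rule:

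- Objectives: "The null hypothesis is that there are no significant differences between patients with adjuvant intake of probiotics" and patients on control lozenges, over a list of outcomes headed by the Gingival Index. No direction is given.
- Statistical methods: "The significance level is set to 5%; confidence intervals are two-sided with a length of 95"%. The WRT is listed among the applicable tests, without a side.

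The one-sided choice appears only in the sample size calculation. It is not justified there or elsewhere, and nothing links it to the two-sided interval.

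**The concern.** The rule for declaring success on the primary endpoint can be read in two ways, and neither fits the whole document.

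- If the test is one-sided at 5%, as in the sample size calculation, it corresponds to a two-sided 90% interval, not the 95% interval to be reported. The test and the interval could then give different answers for the same result.
- If the test is two-sided at 5%, which a reader could take from the non-directional null and the two-sided intervals, the test and the interval agree, but the sample size was computed for a less demanding test and the stated power is too high.

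With about 16 per arm, a result in the gap between the two rules is realistic. Unless the side is fixed beforehand, such a result could be reported either way. Trial status says that no data have been analysed so far, so the choice can still be made without knowledge of the results.

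**Working it through.** **Inputs (Sample size section).** Effect size d = 1.00 SD; alpha 0.05, one-sided; t-test power 0.85; a 5-point allowance from t-test to WRT; 16 per arm evaluable, 17 per arm recruited. Allocation is 1:1 (Sequence generation).

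**Formula.** For n per arm, df = 2n − 2 and the noncentrality is d·√(n/2). Power is the probability that a noncentral t variable exceeds the critical value: t(0.95; df) for one-sided 5%, t(0.975; df) for two-sided 5%. In the two-sided case the chance of rejecting in the wrong direction is negligible. This is the calculation behind R's power.t.test, which the article names. The formula printed in the article lacks the factor 2 for two groups; with normal quantiles it would give (1.645 + 1.036)² ≈ 7.2 per arm. The stated 16 was therefore not obtained from it, and the slip does not affect this point.

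**1. The plan's own figure.** One-sided 0.05, power 0.85, d = 1: n = 15.10, so 16 per arm. Then 32/0.95 = 33.7, so 34. Both stated figures reproduce.

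**2. Power at 16 per arm (df = 30, noncentrality √8 = 2.828).**

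- One-sided 5%: critical value 1.697, power 86.8%.
- Two-sided 5%: critical value 2.042, power 78.1%.

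**3. WRT.** Two routes are used: the article's 5-point deduction, and simulation with exact critical values, normal data, a 1 SD shift and no ties.

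| Evaluable per arm | Test | t-test | t-test minus 5 points | WRT simulated |
|---|---|---|---|---|
| 16 | one-sided 5% | 86.8% | 81.8% | about 84% |
| 16 | two-sided 5% | 78.1% | 73.1% | about 75% |
| 17 | two-sided 5% | 80.7% | 75.7% | about 78% |

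The article claims 85% for the t-test and at least 80% for the WRT. The one-sided row meets both. Neither two-sided row meets either, even with no drop-out.

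**4. Size of the gap.** Two-sided, 85% t-test power needs n = 18.97, so 19 per arm (38 evaluable; 38/0.95 = 40 recruited per age group). At 16 per arm the effect detectable with 80% t-test power is 0.90 SD one-sided and 1.02 SD two-sided, the latter just above the planning effect of 1.00 SD.

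**5. Test against interval.** A one-sided 5% test rejects when the effect favours the probiotic and the two-sided p is below 0.10. A 95% interval derived from the same test excludes no effect only when the two-sided p is below 0.05. For 0.05 < p < 0.10 in the favourable direction, the test declares superiority while the interval includes no effect. In the unfavourable direction the one-sided test does not reject, so this conflict does not arise.

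**The case against.** The strongest reply is that the document gives only one side for a test, and gives it openly: one-sided, superiority, alpha 0.05. The 5% level under Statistical methods agrees with that alpha, and in that sentence the term two-sided describes only the intervals. The null under Objectives is a single sentence covering many outcomes, and the sample size section itself sets a null of no difference beside a one-sided test, so the wording does not prove that a two-sided test was meant. Nor does any section say that the interval decides significance; the WRT does. On this reading the stated power is met, and the remaining mismatch is one of reporting convention.

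Most of this stands. A reader might infer that the sample size is miscalculated, or that the trial fails to deliver its claimed power. The document does not support either: 16 per arm is correct for the test named, and the shortfall appears only under a two-sided 5% standard that no section explicitly assigns to the primary test. A two-sided test is also not the only consistent repair; a justified one-sided test reported with a matching interval would remove the contradiction too.

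The reply does not remove the mismatch itself. The section that sets the level and intervals leaves the side of the deciding test open, the one-sided 5% level is never justified, and it does not correspond to a 95% interval.

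**Conclusion.** The point holds as an inconsistency, not as an arithmetic error. The primary test as sized and the interval as reported use different error rates, and a favourable result with a two-sided p between 0.05 and 0.10 would be read differently by each. Conditional on a two-sided 5% test, power for 1 SD at 16 per arm is 78% (t-test) and about 73–75% (WRT). That is about 7 points below the stated 85%, and 5 to 7 points below the stated 80%. If all 17 per arm are evaluable, the figures are 81% and about 78%.

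These figures take the planning effect of 1.00 SD as given. The simulated WRT values assume normal data without ties, whereas the article says normality cannot be assumed; actual power may differ in either direction. The conflict between test and interval assumes that the interval is derived from the same test.

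This should be corrected, but it does not invalidate the design: the loss is moderate and conditional, and the number of participants need not change.

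**What to change.** Before any data are analysed, state under Sample size and Statistical methods that the primary WRT is two-sided at 5% (equivalently one-sided at 2.5% for superiority of the probiotic), consistent with the two-sided 95% interval. Keep 16 evaluable and 17 recruited per arm in each age group. Restate the power for a 1 SD effect at 16 per arm as about 78% for the t-test and about 73–75% for the WRT, in place of 85% and at least 80%.

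The cost is a few sentences and a less favourable stated power. No additional participants are needed. Keeping the stated 85% under a two-sided test would take 19 evaluable per arm, or 40 recruited per age group instead of 34; this is not required to resolve the inconsistency.

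### The primary superiority test uses a per-protocol set defined by post-randomisation compliance and a deviation list that is still open, so randomisation does not protect the comparison

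*Protocol article*

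**What the plan says.** Each age group is a separate two-arm trial with 1:1 allocation and 34 participants. The primary endpoint is the change in GI from baseline to week 4. The Sample size section sets a one-sided superiority test at alpha 0.05 and names the test: "Hence a Wilcoxon rank-sum test (WRT) is used to decide for significance". The same section fixes the population: "The analysis of the primary endpoint is applied to the per-protocol population".

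The Statistical methods section defines three nested sets:

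- The safety set is everyone exposed to a study intervention at least once.
- The full analysis set (FAS) is a part of that: "The FAS is the subset of subjects in the SES for whom the primary endpoint is available", meaning GI at both baseline and week 4.
- The per-protocol set (PPS) is the FAS without major deviations. On these the section says: "One major protocol deviation is the noncompliant intake of lozenge. Further major protocol deviations may be defined during the study".

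On reporting the other sets it says: "If these populations have remarkably different size, all endpoints and demographics are reported for each population". No size difference is given that would trigger this.

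Two further sections remove randomised participants. Under the criteria for discontinuing or modifying interventions, participation ends if a participant stops the lozenges for any reason or comes to meet an exclusion criterion. Under adverse event reporting, participation is cancelled after an adverse event.

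**The concern.** In a superiority trial, the comparison of groups as randomised is what makes a small p-value evidence about the product. Compliance is observed after randomisation. It may depend on the lozenge received, through taste, tolerability or adverse events. It may also depend on how carefully a participant looks after their mouth: the Intervention description ties each lozenge to tooth brushing, so poor takers may also be poor brushers with worse GI. If such participants leave one arm more often than the other, the groups compared are no longer alike apart from treatment.

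Three features make this harder to detect or correct. The deviation list can grow during the study, and nothing says that this is done without knowledge of allocation or results. The FAS is limited to completers, so no defined set contains all randomised participants. The other sets are reported according to how many are excluded, while the bias depends on who is excluded.

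The choice also fits poorly with the stated purpose. The Abstract speaks of effectiveness, and the Background aims at preventive strategies for daily practice, where some patients will take the lozenges irregularly.

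**Working it through.** **1. The plan's own figure.** Inputs from Sample size: effect 1 SD, one-sided alpha 0.05, power 0.85, two-sample t-test. Exact power for n per arm is 1 − F(t₀.₉₅; 2n−2, d√(n/2)), where F is the noncentral t distribution function, t₀.₉₅ is the 95% point of the central t with 2n−2 degrees of freedom, and d = 1.

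- n = 15: 0.848
- n = 16: 0.868

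This agrees with the article: "The sample size calculation yielded as a result 16 study participants per arm, i.e. 32 participants in total". Adding 5% drop-out gives 32/0.95 = 33.7, so 34, or 17 per arm. The two extra participants cover drop-out by week 4 only, not compliance exclusions. If the PPS fell to 14 or 12 per arm, t-test power would be 0.824 or 0.767.

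**2. Effect of exclusions on the false-positive rate.** The article gives no compliance figures, so these inputs are assumptions. GI change is simulated as normal with no treatment effect, 17 per arm. Each participant has a latent tendency to be excluded that correlates r with GI worsening. The k participants highest on it are removed, and a one-sided 5% Wilcoxon rank-sum test is applied (40,000 runs per scenario for most rows).

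| Excluded (test / control) | r | Rejections |
|---|---|---|
| 1–4 / 0 | 0 | about 5% |
| 1 / 0 | 0.3; 0.5 | 5.8%; 6.1% |
| 2 / 0 | 0.3; 0.5 | 6.9%; 8.3% |
| 3 / 0 | 0.3; 0.5 | 7.9%; 10.9% |
| 2 / 2 | 0.5 | 5.3–5.5% (two separate runs) |
| 0 / 2 | 0.5 | about 3% |

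With three test-arm exclusions and r = 0.5, the mean difference is shifted by −0.15 SD in favour of the product. With exclusions from the control arm only, the shift goes against it.

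**3. Effect of an open deviation list.** Suppose several definitions are tried, each removing two per arm at random, and the best result is kept. The false-positive rate is 6.9% with two definitions, 8.0% with three and 10.0% with five. This requires a choice made after seeing results, which the article neither plans nor rules out.

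**4. Power of an all-randomised analysis.** Assume a share f of the active arm gets no effect, so d = 1 − f. With 17 per arm:

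| f | d | t-test power | n per arm for 85% |
|---|---|---|---|
| 0 | 1.00 | 0.886 | 16 |
| 5% | 0.95 | 0.857 | 17 |
| 10% | 0.90 | 0.822 | 19 |
| 20% | 0.80 | 0.738 | 24 |

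**The case against.** The strongest case against is that nothing here shows the error rate will be wrong. Participants, raters and clinic staff are blinded, the boxes are identical, and only the lab manager knows the allocation. No interim analysis is planned and no data had been analysed at publication. If few are excluded, or the exclusions are alike in both arms, the PPS result will have close to its nominal error rate. Exclusions from the control arm would make the test conservative.

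Most of this stands. A reader might infer that the randomised comparison is lost and that the p-value no longer has its nominal level. The article does not support that. Inflation needs exclusions that both differ by arm and relate to GI, or a choice of definition after seeing results. The figures of 7–11% come only from scenarios that remove test-arm participants alone.

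Blinding does not dispose of the point, however. Adverse events and stopping can differ by arm in a blinded trial, unblinding after an adverse event is allowed, and the article does not say that deviations are defined or assigned blind.

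A second objection is that an analysis plan not shown here may hold the deviation list and a numeric compliance threshold. That also stands, and their absence from the article is not held against it. But the article itself fixes the per-protocol set as primary, allows deviations to be added during the study, and makes reporting of the other sets conditional.

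**Conclusion.** The point holds as a defect in a stated rule. The sole confirmatory test in each age group is committed to a set selected after randomisation, with no all-randomised analysis defined and no firm commitment to report any other set. Protection by randomisation is given up, and how much that matters cannot be known in advance.

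Under the assumptions shown, the one-sided 5% level could lie anywhere from about 3% to about 11%, and stays near 5% when exclusions are balanced or unrelated to outcome. These are illustrations of direction and scale, because the exclusion counts and correlations are assumed. Making the FAS primary as now defined would not fully repair this, since it contains completers only.

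**What to change.** - **Population.** Make all randomised participants, analysed as allocated, the primary population, and redefine the FAS accordingly.
- **Follow-up.** Keep collecting GI at the routine orthodontic visits, where consent allows, from participants who stop lozenges. The sections that end participation on lozenge stopping, a newly met exclusion criterion or an adverse event must be reconciled with this. It concerns data collection only.
- **Missing week-4 GI.** State in advance a method compatible with the rank-sum test, for example multiple imputation from the available GI visits with a stated pooling rule. This replaces leaving a missed visit out of the evaluation.
- **Supportive analysis.** Always report the PPS, whatever the set sizes.
- **Deviations.** Replace the permission to add deviations during the study with a list closed before unblinding.

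The cost is more than wording, because follow-up after discontinuation is a small operational change in a trial already recruiting. There is also some dilution: with 17 per arm, t-test power stays above the planned 0.85 if 5% of the active arm get no effect, but falls to 0.822 at 10% and 0.738 at 20%. Planned numbers should be looked at again if poor compliance is expected.
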